# The NExT trial: Protocol for a two-phase randomized controlled trial testing transcranial magnetic stimulation to augment exposure therapy for youth with OCD

**DOI:** 10.1186/s13063-024-08629-1

**Published:** 2024-12-18

**Keywords:** Transcranial magnetic stimulation, Neuromodulation, Cognitive Behavioral Therapy, OCD, Exposure therapy

## Abstract

**Background:**

Exposure with Response Prevention (ERP) is a first-line treatment for OCD, but even when combined with first-line medications it is insufficiently effective for approximately half of patients. Compulsivity in OCD is thought to arise from an imbalance of two distinct neural circuits associated with specific subregions of striatum. Targeted modulation of these circuits via key cortical nodes (dorsolateral prefrontal cortex [dlPFC] or presupplementary motor area [pSMA]) has the potential to improve ERP efficacy by decreasing compulsions during therapy.

**Methods:**

The NExT (Neuromodulation + Exposure Therapy) trial is a two-phase, multisite early-stage randomized controlled trial designed to examine whether TMS augmentation of ERP alters activity in dlPFC and/or pSMA-associated circuitry and reduces compulsions during therapy in youth with OCD age 12–21 years. Phase 1 (*N* = 60) will compare two different active TMS regimens with sham: A. continuous theta burst stimulation (cTBS) to pSMA vs. B. intermittent theta burst stimulation (iTBS) to dlPFC. A priori “Go/No-Go” criteria will inform a decision to proceed to Phase 2 and the choice of TMS regimen. Phase 2 (*N* = 60) will compare the selected TMS regimen vs. sham in a new sample.

**Discussion:**

This trial is the first to test TMS augmentation of ERP in youth with OCD. Results will inform the potential of TMS to enhance ERP efficacy and enhance knowledge about mechanisms of change.

**Trial registration:**

ClinicalTrials.gov NCT05931913. Registered prospectively on July 5, 2023.

## Administrative information

Note: the numbers in curly brackets in this protocol refer to SPIRIT checklist item numbers. The order of the items has been modified to group similar items (see http://www.equator-network.org/reporting-guidelines/spirit-2013-statement-defining-standard-protocol-items-for-clinical-trials/).

**Table Taba:** 

Title {1}	The NExT trial: Protocol for a two-phase randomized controlled trial testing transcranial magnetic stimulation to augment exposure therapy for youth with OCD
Trial registration {2a and 2b}.	ClinicalTrials.gov Identifier: NCT05931913
Protocol version {3}	September 20, 2023 Protocol version 1
Funding {4}	This research is supported by the US National Institutes of Health (1R61MH133666-01, PIs: [name]; 5P20GM130452).

## Introduction

### Background and rationale {6a}

Obsessive–compulsive disorder (OCD) is a serious mental illness characterized by obsessions (intrusive thoughts or images that cause intense distress) and compulsions (actions designed to neutralize obsession-related distress). OCD affects 2–3% of youth and can cause significant impairments in social, academic, and familial functioning [1]. Symptoms remain chronic without treatment [2]. Exposure therapy (in the form of exposure plus response prevention; ERP) is an efficacious first-line therapy alone or in combination with serotonin reuptake inhibitors (SRI) for pediatric OCD [3]. However, many youth remain symptomatic following treatment, with only 53.6% achieving clinical remission in combined treatment, 39.3% in ERP alone, and 21.4–30.0% in SRI alone [3, 4]. There is a pressing need for augmentation strategies to improve these outcomes, and neuromodulation in particular has been identified as a highly promising method for ERP augmentation [5].

In ERP, youth engage in *exposures*—tasks that involve intentionally approaching obsession-related stimuli that elicit distress (e.g., touching an object perceived as contaminated). During exposures, *response prevention*—the prevention of related compulsions (e.g., hand washing)—is a necessary condition for fear extinction learning, the presumed mechanism of ERP, to occur. Use of strategies to reduce compulsions during exposure tasks predicts better outcomes at post-treatment and 3-month follow-up [6]. Unfortunately, exposure tasks are designed to elicit the urge to engage in compulsions, and resisting this urge can be very difficult for many youth. Improving youth’s ability to prevent compulsions during exposure tasks is a promising approach through which clinical response to ERP might be augmented.

Compulsive behavior is driven by aberrant functioning of cortico-striatal circuits involved in goal-directed vs. habitual action selection [7]. Goal-directed behaviors, which are contingency-sensitive and performed intentionally, depend on dorsomedial striatum (DMS, aka caudate) and its connections to dorsolateral prefrontal cortex (dlPFC). This circuitry shows *diminished* function in OCD, including within-and between-network resting-state hypoconnectivity [8] and local dlPFC hypoactivation during goal-directed planning tasks [9] and symptom provocation [10]. Habitual behaviors are repetitive, sequential behaviors that are contingency-insensitive, and these rely on connections between dorsolateral striatum (DLS, aka putamen) and sensorimotor cortices. This circuitry shows *exaggerated* function in OCD, including hyperactivity of the pre-supplementary motor area (pSMA), orbitofrontal cortex (OFC), DLS, and the pSMA-DLS circuit at rest, during response inhibition, and during symptom provocation (e.g., [10–12]. Collectively, these neural findings converge with behavioral evidence showing overreliance on the habit system relative to the goal-directed system in OCD [13].

Cortical nodes of these circuits (dlPFC, pSMA) have been leading candidates for studies using repetitive transcranial magnetic stimulation (rTMS) to target compulsivity. rTMS is a non-invasive brain stimulation technique that can selectively target cortical nodes of brain circuits in presumed “excitatory” (5 + Hz rTMS or intermittent theta bursting pattern, iTBS) or “inhibitory” directions (1 Hz rTMS or continuous theta bursting pattern, cTBS). rTMS modulates both the cortical node and its connected subcortical structures, [14] making it a useful tool for engaging specific functional brain networks with high resolution. TMS has traditionally been applied as a monotherapy for psychiatric illness. However, a large body of literature confirms that stimulation effects highly depend on the state of the targeted circuitry, [15] leading for calls to improve TMS outcomes with “functional targeting” that combines TMS with behavioral/cognitive engagement of the same circuit being modulated [16].

Enhanced function of DMS-driven circuitry is associated with ERP response in both adult [17] and pediatric [18] OCD. Excitatory stimulation with rTMS over cortical nodes has been linked to improvements in OCD symptoms globally (broad prefrontal cortex, dlPFC, though results are mixed [19]) and to compulsion reduction specifically (left dlPFC [20]). Reduction in the pathologically exaggerated function of DLS-driven habit circuitry is also linked to ERP response [21]. Inhibitory stimulation of pSMA with rTMS has been shown to reduce severity of OCD (e.g., [22]) and tics, [23] and inhibition of orbitofrontal cortex with cTBS reduces compulsive behavior [24].

A head-to-head examination of these rTMS strategies is needed to identify whether it is preferable to “turn up” goal circuitry or “turn down” habit circuitry to reduce compulsions during ERP. A meta-analysis concluded that both inhibitory pSMA stimulation and excitatory left dlPFC stimulation are efficacious for adult OCD, [25] but these have not yet been examined in the same study. The closest approximation is a retrospective chart review that found no difference in response rates for excitatory dlPFC and inhibitory pSMA stimulation [26].

Taken together, the existing literature suggests the hypothesis that augmenting ERP with rTMS to induce more normative/balanced function of circuits supporting goal-directed (dlPFC-DMS) and habitual behavior (pSMA-DLS) will boost response prevention, leading to enhanced ERP efficacy. Accordingly, we designed the NExT trial, an NIMH-funded two-phase, milestone-driven early-stage randomized controlled trial. To our knowledge, this will be the first treatment trial of rTMS for youth with OCD. Here, we describe the trial protocol.

### Objectives {7}

The overall objective of this two-phase study sequence is to test whether augmenting ERP with rTMS over cortical nodes of select cortico-striatal circuits changes circuit connectivity and enhances response prevention during exposure in youth with OCD. Phase 1 will test two rTMS strategies. In one, we will attempt to “turn down” overactive habit circuitry by delivering continuous theta burst stimulation (cTBS) to the pSMA. In the other, we will attempt to “turn up” underactive goal-directed circuitry by delivering intermittent theta burst stimulation (iTBS) to left dlPFC. Analyses will focus on testing changes in neural (fMRI-measured resting state functional connectivity; RSFC) and behavioral (rate of compulsions during ERP) outcomes.

We will proceed to Phase 2 if the following are demonstrated: (1) one or both active rTMS conditions demonstrate neural change (within- and between-subject effect size ≥ *d* = 0.3) in the targeted circuit post-treatment (pSMA-DLS for cTBS arm, dlPFC-DMS for iTBS arm); (2) evidence of safety (≤ 20% rate of TMS-related adverse events); and (3) evidence of feasibility (≥ 80% treatment completion rate). If these criteria are met, we will select a TMS regimen for phase 2 using the following rules: (1) if only one active condition meets the above criteria, that condition wins; (2) if both conditions meet criteria, the condition with lowest rate of compulsions during ERP wins.

The primary objective of Phase 2 is to replicate and validate Phase 1 findings for the optimal TMS regimen. Phase 2 will also test the link between neural/behavioral target engagement (change in RSFC and compulsions during ERP) and functional outcomes (OCD symptom change) at post-treatment. We will explore subgroup differences (e.g., based on OCD symptom subtype) and durability of treatment effects (at 1-month follow-up) in these primary outcomes. We will also explore the relationships between performance on computerized neurocognitive tasks with OCD symptom improvement.

### Trial design {8}

Both phases are randomized, sham-controlled, double-masked, parallel-group, superiority trials. Phase 1 is a three-arm trial (sham, cTBS to pSMA, or iTBS to dlPFC; *n* = 20 per group), and phase 2 is a two-arm trial (sham or active stimulation; *n* = 30 per group; Fig. 1). Randomization in both phases will be blocked on site (Brown University or University of Minnesota) and symptom severity (Children’s or adult Yale-Brown Obsessive Compulsive Scale score above or below 32, indicating the cutoff for “extreme” symptoms). Participants have a 2 in 3 chance of being assigned to an active TMS treatment arm.

**Fig. 1 Fig1:**
[figure not shown]
Flow chart of each study phase

## Methods: participants, interventions and outcomes

### Study setting {9}

The study will occur in an outpatient clinical-research setting at two collaborating sites: the University of Minnesota (UMN) and Brown University (Brown). The “Brown” site encompasses two affiliated hospital sites in the Brown University Medical School system (Butler Hospital and Bradley Hospital).

## Eligibility criteria {10}

### Eligibility determination

Study staff will pre-screen interested participants over the phone for inclusion/exclusion criteria, including safety screening (Gate A). Relevant medical records will be reviewed by a study physician to assess initial eligibility. The clinical interview (Gate B) will include informed consent and a full clinical interview to determine final eligibility.

### Inclusion/exclusion criteria

The following are inclusion criteria: (1) age 12–21 years at the time of enrollment; (2) current OCD according to DSM-5 criteria; (3) score of ≥ 16 on the Children’s or adult Yale-Brown Obsessive Compulsive Scale (C/YBOCS), indicating OCD symptoms of moderate or greater severity; (4) presence of motor compulsions on CY-BOCS compulsion checklist; (5) participant and at least one parent (for participants < 18) are English-speaking, to ensure comprehension of informed consent and study measures and instructions; (6) medication stability for participants ≥ 6 weeks with no planned changes during the 3-week intervention protocol for those taking psychotropic medication.

The following are exclusion criteria: (1) personal or family history in a first-born relative of a medical condition judged by a study physician to impact the risk profile of TMS or participant’s ability to engage in the study; some examples include epilepsy or seizure disorder(s), bipolar disorder/mania, intracranial pathology, traumatic brain injury, brain tumor, stroke, implanted medical devices, or moderate-severe heart disease; (2) current pregnancy or youth of childbearing age not using effective contraception; (3) inability to undergo MRI; (4) left handedness; (6) active suicidality; (7) history or risk for neurocardiogenic syncope; (8) concurrent psychotherapy of any kind for OCD; (9) concurrent TMS or receipt of any TMS experimental or clinical treatment less than 3 months prior to enrollment; and (10) taking a medication deemed to pose high seizurogenic potential per physician review.

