### Adverse event reporting and harms {22}

The Adverse Events Questionnaire (AEQ) will be administered at every TMS study visit, and staff will conduct general inquiries regarding health status between visits. For each endorsed AE, data will indicate severity, relatedness to TMS, relatedness to ERP, and actions taken. All adverse events will be reviewed by the PIs. AE reporting procedures are in accordance with policies of the IRB, FDA, NIH, and site institutions. Annual IRB progress reports will include (1) adverse events deemed expected or unrelated to the study and (2) protocol deviations that do not affect the scientific soundness of the research plans or the rights, safety, or welfare of the human subjects. Promptly reportable events include (1) unanticipated serious adverse events, (2) unanticipated problems involving risks to subjects or others related to research participation, (3) information reports indicating new or increased risk with the investigational device, and (4) protocol deviations that increased risk of harm.

The study will be stopped should any of the following occur: (1) two participants experience a generalized-onset seizure, (2) two participants experience a focal-onset seizure with impaired awareness, (3) two participants experience a seizure for which anticonvulsant medication is administered, (4) one participant experiences status epilepticus or is hospitalized due to a seizure(s), (5) two or more participants attempt suicide or one participant completes suicide, (6) two or more device-related serious adverse events (SAEs) in one or more participants; OR a single device-related SAE in five or more participants, or (7) two or more participants show a decrease in working memory at any time during the study. The likelihood of a seizure occurring in this trial is extremely low given the TMS parameters being used and the design of inclusion/exclusion criteria to exclude participants with elevated risk [45].

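### Exclusion (1) defines the relatives whose history counts by birth order (first-born), which is not a degree of kinship and cannot be applied as a screening rule

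*Protocol article*

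**What the plan says.** In the protocol article, Inclusion/exclusion criteria, exclusion (1) applies to "personal or family history in a first-born relative of a medical condition judged by a study physician to impact the risk profile of TMS" or on the participant's ability to take part. The clause then illustrates the conditions meant: "some examples include epilepsy or seizure disorder(s), bipolar disorder/mania, intracranial pathology, traumatic brain injury, brain tumor, stroke", followed by implanted devices and heart disease of at least moderate degree.

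The only other criterion that bears on seizure risk is exclusion (10), "taking a medication deemed to pose high seizurogenic potential per physician review". It concerns the participant's medication and says nothing about relatives.

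Under Eligibility determination, staff pre-screen candidates by phone against the criteria, with a safety screen included. In addition, "Relevant medical records will be reviewed by a study physician to assess initial eligibility". A consent visit with a full clinical interview then settles eligibility. Table 1 lists a TMS/MRI safety screen answered by parent and participant, without giving its items.

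The section Adverse event reporting and harms {22} calls the likelihood of a seizure extremely low and gives two reasons: the stimulation parameters, and "the design of inclusion/exclusion criteria to exclude participants with elevated risk".

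**The concern.** An eligibility rule on family history has to say how close a relative must be. Exclusion (1) says instead where the relative falls in a birth order. Birth order does not measure how closely someone is related to the participant, so the rule as written separates relatives on a feature unrelated to its purpose.

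The clause is operative text, because the phone pre-screen is conducted against these criteria. Staff who meet the phrase must either apply it literally or put their own meaning in its place, and the article does not settle which. Recruitment runs at two sites, one of which comprises two hospitals, so the same family history could be handled in more than one way.

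The criterion also belongs to the trial's safety argument. The harms section relies on the eligibility criteria as one of two grounds for expecting very few seizures, and two participants with a generalized-onset seizure would stop the study.

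**Working it through.** No arithmetic applies. The point depends on no sample size, rate or error level, and the plan gives no figure to reproduce. The check sets the clause against concrete cases and then looks for text elsewhere that would repair it.

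**Step 1. Apply the literal wording.** Take a history of seizure disorder that the study physician judges relevant, and ask whether exclusion (1) is triggered.

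| Person with the history | Triggered as written? |
|---|---|
| The participant | Yes, through the personal-history limb |
| A parent who was an eldest child | Yes |
| A parent who was not an eldest child | No |
| An eldest sibling | Yes |
| Any later-born sibling | No |
| A first-born cousin or more distant first-born relative | Yes |

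The two parents in the table are equally close to the participant, and so are the two siblings, yet each pair is split. The distant relative is included although closer ones are left out. A group of full siblings has only one first-born, so if the participant is the first-born, no full sibling can count. If the phrase is taken to mean only the eldest sibling in the participant's own family, the cousin drops out, but so do both parents. Neither reading yields a degree of kinship.

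**Step 2. Look for a definition or a wider rule elsewhere.**

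- The abbreviations list does not contain the term, and no other section defines it.
- No other exclusion mentions family history. Exclusion (10) is about medication and exclusion (7) about neurocardiogenic syncope.
- The physician's judgement in exclusion (1) attaches to the medical condition. It does not extend to which relatives count.
- Eligibility determination adds a safety screen, record review and an interview. It does not say which relatives' histories these cover.
- Table 1 names the TMS/MRI safety screen but not its family-history content.

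Nothing in the article repairs the wording.

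**Step 3. Trace what the safety argument loses.** The harms section has two grounds.

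| Ground | Affected by the wording? |
|---|---|
| TMS parameters | No |
| Eligibility criteria: participant's own history, exclusion (1) | No |
| Eligibility criteria: seizurogenic medication, exclusion (10) | No |
| Eligibility criteria: relatives' history, exclusion (1) | Yes |

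The defect reaches one component of one of the two grounds.

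**The case against.** The best defence is that this is a one-word slip. Nothing suggests that the investigators chose birth order as a risk marker, and staff trained in TMS would probably read the phrase as a degree of kinship. The article condenses protocol version 1, which is not shown, and the correct term may stand there and on the screening form. Shared standard operating procedures, with one site leading TMS across both, make divergent screening less likely. All of this stands and limits the weight of the point. It does not make the published criterion correct, and the safeguards that might compensate are not described as covering a wider set of relatives.

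A reader might also infer several stronger things that the document does not support:

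- *That the criterion misses most close relatives.* It misses some under the literal wording. In many families a parent or an older sibling is first-born and counts, and the article gives nothing from which to estimate a proportion.
- *That the claim of very low seizure likelihood fails.* That claim also rests on the TMS parameters and on parts of the criteria that the wording does not touch.
- *That the clause would exclude someone for a relative's implant or head injury.* The listed conditions are examples, subject to the physician's judgement that they matter for this participant, and that judgement would filter such cases out.
- *That a criterion has been lost because the numbering runs from (4) to (6).* A numbering error is enough to explain the gap. It deserves a check but adds no weight here.

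**Conclusion.** The concern holds as a wording error in a safety-relevant eligibility criterion. As written, exclusion (1) sorts relatives by birth order, leaves out parents and siblings who are not first-born, and admits distant relatives who are. It is the only criterion that names epilepsy or seizure disorder and the only one that deals with family history.

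The size in participants cannot be derived from the document. The effect in practice may be small or nil if the safety screen, record review and interview ask about close relatives regardless of birth order. The conclusion assumes only that the words carry their ordinary meaning and that the article reproduces the criterion in use. If the full protocol has a proper kinship term, the error is confined to the publication. The finding is not evidence that participants have been or will be wrongly enrolled, and it has no bearing on the analysis.

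**What to change.** The sponsor should replace *first-born relative* with the degree of kinship intended, apparently first-degree, and confirm that this is what was meant. The same term should stand in the article, the full protocol and the phone-screening form used at both sites.

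The choice of which conditions matter should stay with the study physician, as the clause now provides. Narrowing the family-history limb to a fixed set of conditions would be a new clinical rule for which the document gives no basis. While the list is open, the sponsor should check the missing number (5) and either renumber or restore the item.

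The cost is a text correction, with no added procedure, visit or data item. If the error also stands in the operative protocol, the change goes through the IRB approval that the article requires before any protocol change.

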### Individuals who will perform the interventions

TMS operators will be trained according to recommended training guidelines [27]. ERP therapists will be individuals who have completed evidence-based training in the delivery of ERP for OCD across the lifespan [28] and are additionally trained in this study protocol. They will receive ongoing supervision from a licensed clinician with ERP expertise.

